# Pulmonary rehabilitation in patients with mustard gas lung disease: a study protocol for a randomized controlled trial

**DOI:** 10.1186/s13063-019-3180-3

**Published:** 2019-02-14

**Keywords:** Pulmonary rehabilitation, Chemical warfare, Mustard gas, Randomized controlled trial

## Abstract

**Background:**

More than 60,000 people have health problems due to chemical weapons exposure during the Iran–Iraq war. Respiratory consequences of mustard gas exposure are common and disabling; medical interventions have limited effect. Patients complain of cough, sputum, breathlessness and exercise limitation. We hypothesized that patients with this condition would benefit from pulmonary rehabilitation.

**Methods:**

We outline the protocol for an assessor-blind, two-armed, parallel-design randomized controlled clinical trial (IRCT2016051127848N1). Sixty patients with respiratory disease due to documented sulfur mustard gas exposure will be randomized to either take part in a 6-week pulmonary rehabilitation programme or receive usual care. Inclusion criteria include forced expiratory volume in 1 second < 80% predicted and Medical Research Council dyspnoea score ≥ 3. The primary endpoint will be the change in cycle endurance time at 70% baseline exercise capacity at 6 weeks. Lung function, physical activity, the strength and endurance of the quadriceps muscle, and quality of life will also be compared. Outcomes will be assessed at 6 weeks and 12 months. Health care utilization will also be assessed.

**Discussion:**

If the study confirms that rehabilitation is effective for patients with mustard gas lung disease this should prompt provision of the intervention to this patient group.

**Trial registration:**

Iranian Registry of Clinical Trials, IRCT2016051127848N1. Registered on 24 May 2016.

**Electronic supplementary material:**

The online version of this article (10.1186/s13063-019-3180-3) contains supplementary material, which is available to authorized users.

## Background

There are more than 60,000 victims of chemical weapons used against Iranian combatants and civilians during the Iran–Iraq war in the 1980s [1]. Mustard gas has well-described respiratory complications, including tracheal stenosis, tracheomalacia, bronchiectasis and constrictive bronchiolitis [2–4]. Patients experience cough, sputum and breathlessness associated with limitation of their exercise capacity and difficulties with day-to-day activities. Fatigue, anxiety and depression are also common [5, 6]. Clinical symptoms and quality of life are in some studies only poorly correlated with pulmonary function [7]. The clinical picture is thus similar to that observed in chronic obstructive pulmonary disease (COPD) [8].

Exercise capacity and breathlessness in lung disease can be influenced by a combination of cardiorespiratory impairment, skeletal muscle dysfunction and changes to the threshold at which symptoms are tolerated [9, 10]. Breathlessness, like pain, can be modified by past experience and expectations, and there is evidence of central adaptations in people with lung disease [10, 11]. A vicious cycle of breathlessness, immobility and deconditioning can worsen the patients’ condition and make them more susceptible to the development of physical inactivity-related multimorbidity including hypertension, diabetes and osteoporosis. Most of the people exposed to mustard gas in the 1980s are now in their 50s or older [1]. A sustainable health system needs to prevent the development of future health problems—physical activity interventions have a key role in this [12].

Pulmonary rehabilitation (PR) is a holistic approach for people limited by lung disease, defined as ‘a comprehensive intervention based on a thorough patient assessment followed by patient-tailored therapies that include, but are not limited to, exercise training, education on your lung disease or condition and how to manage it, and behaviour change, designed to improve the physical and psychological condition of people with chronic respiratory disease and to promote the long-term adherence to health-enhancing behaviours’ [13]. There is an extensive evidence base for PR in COPD patients [14] and a growing body of research in other lung diseases [13]. PR can improve muscle strength, exercise capacity, health status and symptoms of anxiety and depression as well as reducing hospital readmission rates [13]. It has been shown to alter breathlessness perception [10] and also boosts COPD patients’ understanding of their condition and ability to self-manage.

Skeletal muscle impairment is a common feature of COPD and other lung diseases such as pulmonary fibrosis [15]. It can occur early in COPD; weakness is present in about 30% of patients and is associated with reduced levels of physical activity [16]. It directly influences exercise performance [17], is associated with poor health status [18] and is an independent predictor of health care utilization [19] and mortality [20]. Musculoskeletal disorders are also highly prevalent in COPD [21].

A marked increase in susceptibility to fatigue is also observed in COPD, with a more rapid decline in performance during continuous or repeated bouts of exercise [22] or with non-volitional testing [23]. This is associated with a fibre type shift [24], reduced oxidative capacity [23, 24] and increased skeletal muscle adiposity [25]. This fibre type shift is itself independently associated with increased mortality risk [26].

Although the disease shares many clinical features with COPD, few data exist on skeletal muscle parameters in patients with mustard gas lung disease. It is likely that similar processes are in place. In spite of inhaled and other therapies, the clinical condition of chemical warfare victims is progressing with time and as they age [3]. We hypothesize that, as is the case in COPD patients, pulmonary rehabilitation will improve the health of this patient group. To address this, we will conduct a randomized controlled trial to address the following key questions: does PR improve exercise capacity; does PR improve health status; does PR influence daily physical activity levels; does PR increase quadriceps strength; does PR increase quadriceps cross-sectional area; and does PR reduce health resource utilization?. In order to improve the completeness of trial protocols, we used SPIRIT 2013 Checklist (Additional file 1).

## Methods

### Study design

We have designed an assessor-blind, parallel-group, randomized clinical trial comparing PR with usual care to assess the effect of this intervention in mustard lung patients (Fig 1).

**Fig. 1 Fig1:**
[figure not shown]
Flow diagram of recruitment, intervention, follow-ups and assessment. Procedure of the study evaluating the impact of the pulmonary rehabilitation programme. 6MWT six-minute walk test, FFM fat-free mass, RF csa rectus femoris cross-sectional area, PFTs pulmonary function tests, QMVC quadriceps maximal voluntary contraction

### Study setting

The pulmonary rehabilitation, trial activities and other clinical services will be delivered in Tehran’s Khatam-ol-Anbia Hospital. This hospital is a sub-specialized centre equipped with specialized personnel and advanced equipment including a cardiopulmonary rehabilitation hall. It is located in the city centre which makes it easier to access. Moreover, one of the missions of this hospital is to deliver specialized and sub-specialized services to war veterans [27].

### Participants

The participants are chemical warfare victims with contemporaneously documented exposure to mustard gas, residing in Tehran and its suburbs, who have symptomatic lung disease. Inclusion criteria include FEV_1_ < 80% and MRC dyspnoea score ≥ 3 [28].

Exclusion criteria are: any type of debilitating clinical condition that prevents the patient from participating in the rehabilitation programme, such as arthritis; any type of clinical condition that will endanger the patient during the physical exercises, such as uncontrolled cardiac diseases; the presence of other non-chemical-related pulmonary diseases, like asthma; active malignancy; and severe cognitive disorder and psychiatric disease that is associated with memory disorder.

### Interventions

#### Intervention group

In addition to the usual treatment, the intervention group will receive pulmonary rehabilitation services. The pulmonary rehabilitation intervention will include a combination of physical exercises, an educational programme and psychosocial support. The physical exercises will include endurance and strength components, tailored to each individual’s condition and characteristics, prescribed according to the following protocol. Both the upper and lower limbs will be exercised, although with greater emphasis on the legs. For more details of the intervention protocol, please see Additional file 2.

#### Usual care

The control group will continue on their usual medication with management determined by their clinical team. They will receive standard advice about the importance of physical activity and be encouraged to exercise regularly. The participants in both groups will visit 12 times, at 1-month intervals (Fig. 2).

**Fig. 2 Fig2:**
[figure not shown]
Steps taken at each visit. *Demographics and past medical history. **Dyspnoea scale, fatigue scale, body plethysmography parameters, diffusing capacity/transfer factor of the lung for carbon monoxide parameters, rectus femoris cross-sectional area, incremental cycle exercise test parameters, constant work rate cycle endurance test parameters, isokinetic quadriceps muscle function test parameters, body composition parameters, six-minute walk test parameters, Hospital Anxiety and Depression Scale parameters, St. George’s Respiratory Questionnaire parameters, blood test parameters and daily physical activity parameters. ***Number of exacerbations of the disease, hospitalizations and medications

### Outcomes

#### Outcome assessment

Before starting the outcome assessment, assessors will be trained in and familiar with the assessment protocol and instruments. They will be blind to the study participants’ group allocations. Outcomes will be measured at baseline prior to the intervention, after 6 weeks and after 12 months from study entry.

#### Primary outcome

The primary outcome of the study will be the cycle endurance time at 70% of baseline workload, measured at the end of 6 weeks. An increase of > 105 s in the endurance time has been defined as the minimum clinically important difference and will be used as a threshold for responder analysis [29].

A symptom-limited incremental exercise test (IET) will be used to determine the W_max_ of each participant at baseline. After 3 min of acclimatization and 1 min of unloaded cycling, the workload is increased by 10 W/min until the patient can no longer bear heavier loads. The highest workload that each individual can complete during 60 s of pedalling will be defined as the W_max_ [30]. A practice constant work rate test will be performed approximately 1 h after the IET at 70% maximum workload. Three minutes of unloaded cycling (0 W) will be given to allow for respiratory adaptation and warm up [31]. At the next session, a few days later, the constant workload test will be repeated and the outcome of this taken as the baseline measure of the endurance time [30].

### Secondary outcomes/clinical and behavioural

#### Pulmonary function

Spirometry, body plethysmography and gas transfer (DLco) will be measured in accordance with international guidelines [31–33].

#### Quadriceps strength and endurance

Participants will perform 30 repetitions of a maximum voluntary contraction with an angular velocity of 90° per second using the Isokinetic Test Rehabilitation System (MPS21) in an upright sitting position, with an angle of 90° at the thigh joint [34]. Strength is assessed as the quadriceps muscle peak torque (in Newton-meters). The endurance of the quadriceps muscle is defined as the total work done (Joules) during 30 consecutive muscular contraction repeats [35]. To reduce the effects of learning at the baseline assessment, the test will be performed twice and the best value used.

#### Quadriceps muscle bulk

The rectus femoris cross-sectional area (RFCSA) will be measured with B-mode ultrasonography using an 8-MHz, 5.6-cm linear probe, similar to de Bruin et al.’s method [36]. The probe will be placed perpendicular to the longitudinal axis of the thigh in the superior segment, three-fifths of the distance from the anterior superior iliac spine to the superior patellar border. The highest point of the thigh from the RFCSA can be viewed in one field in all individuals. The other quadriceps muscles cannot be investigated by this method. Imaging will be done when the leg is at rest and in a condition wherein the individual is lying supine. Oblique imaging will be minimized by the operator to achieve the smallest cross-sectional image. The depth of the scan is set to where the femur alignment can be recognized. The contraction–relaxation manoeuvre will be used to delineate the muscle septa before the image is taken. Once the inner echogenic line of the rectus femoris is delineated by a movable cursor on a frozen image, the RFCSA will be calculated using a planimetric technique [16, 37]. This outcome will be assessed three times, at baseline, the 6th week and the 12th month.

#### Six-minute walk distance

The 6MWT is done in accordance with ATS guidelines [38], including a practice walk. The better test will be considered the patient’s baseline assessment. The patients will not do warm-ups before the test and will rest for at least 10 min before the test is begun. Any contraindications to the test will be sought. The blood pressure, heart rate and SpO_2_, as well as dyspnoea and leg fatigue with the Borg scale, will be recorded. Patients will receive standard instructions on going the greatest distance during 6 min. They will be monitored throughout the test for SpO_2_. If a pause is required due to dyspnoea or fatigue, the patient will be allowed to rest. However, the chronometer will not be stopped and the numbers and durations of stops will be noted.

At the end of the 6 min, in addition to registering the distance walked, the SpO_2_ and heart rate will be measured, and the level of dyspnoea and leg fatigue will be measured with the Borg scale.

#### Daily physical activity

Daily physical activity will be measured with an accelerometer (triaxial pedometer PD724; Tanita, Tokyo, Japan). The patient will use the pedometer according to instructions for a week at three stages: a week before they start the programme at baseline, the 6th week and the 12th month. Participants will be asked to bring the pedometer after a week. The Tanita PD724 pedometer displays a cumulative step count for each day and also retains the step counts from the preceding 7 days in its memory, allowing the average step count for the preceding week to be evaluated [39]. The first and last days of handing over the pedometer will not be included in the estimations due to the possibility of bias.

#### Quality of life

St. George’s Respiratory Questionnaire (SGRQ) is a standard self-administered questionnaire that has been specifically designed to assess QOL in patients with chronic respiratory diseases [40]. The Persian version has also been standardized and domesticized, and can be used to evaluate QOL in patients with chronic pulmonary diseases [41]. This tool consists of three sections: symptom, activity and impact. In the first section, the symptoms are assessed, and items such as the frequency of cough, sputum production, wheeze, breathlessness and duration and frequency of attacks of breathlessness or wheeze are evaluated. Activity and impact are examined in the next sections and include the activities that bring about breathlessness, or the activities that are limited due to breathlessness. Moreover, the impact of respiratory problems on life and activities such as employment, daily life disorders and so forth are evaluated [41].

#### Anxiety and depression

The HADS questionnaire is a well-known tool to screen for anxiety and depression, and can detect the impact of therapeutic interventions. Studies conducted on the validity of this questionnaire in detecting the symptoms and causes of anxiety and depression and assessing their severity have indicated its high accuracy and high validity. The Persian version has also been standardized and domesticized, and can be used [42]. This tool contains seven questions for assessing anxiety and seven questions for assessing depression, scored from 0 to 3. Thus, each individual can gain 0–21 for anxiety or depression [43]. Based on the results of a systematic review on a number of studies employing this tool, the cut-off point for anxiety or depression is 8/21 [44].

#### Body composition

The participants will be asked to stand barefoot while their height is measured to the nearest 0.5 cm. A single-frequency bioelectrical impedance analyser (BIA) will be used to assess body composition. Height (cm), weight (kg), FFM (kg) and BMI (kg/m^2^) will be measured at baseline, the 6th week and the 12th month.

#### Blood tests

Testosterone, high-sensitivity CRP, IGF-1 and GH will be measured as factors that may be associated with reduced muscle mass. These tests will be measured at baseline, the 6th week and the 12th month.

#### Number of disease exacerbations and hospitalizations

To measure this outcome, the number of exacerbations of disease and cases of hospitalizations due to pulmonary disease during the past year will be asked. An exacerbation is defined as ‘an increase in respiratory signs and symptoms leading to change in type and/or rate of medicine intake’. This outcome will be assessed based on recall and clinical records at baseline, the 6th week and the 12th month. Heath resource utilization will be assessed from a health service perspective. Data will be captured from central clinical records and include hospital visits, medication and medical procedures performed. These will be related to standard costs to allow for an estimate of the health economic impact of the intervention to be assessed.

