### Randomization

After selecting the participants according to the inclusion and exclusion criteria, baseline assessments will be performed. The participants will then be randomized into control or intervention groups. A random sequence will be determined from the randomization website (http://www.jerrydallal.com/random/permute.htm) in blocks of four. Randomization will be performed by a technician who is blind to the title of each group. In order to protect confidentiality in all stages of the trial, each participant will be assigned a unique identification code.

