### Sample size and statistical analysis

Assuming a 105-s improvement in the time limit in the treatment arm and a 20-s improvement in controls with an SD of 100, 90% power and a significance level of 5% requires 60 patients to complete the study.

The data will be cleaned and assessed for outliers and missing variables. Outcomes will be compared using ANOVA adjusted for baseline parameters. The data will be analysed by *t* test, chi-square test and, if required, non-parametric tests and with Excel 2010 and SPSS Statistics 20 software at a level of significance of 0.05.

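### The week-6 count of exacerbations and hospitalisations looks back a full year, so about 88% of its window precedes randomisation and a weak comparison loses further precision

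*Protocol article*

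**What the plan says.** The secondary-outcome section on exacerbations and hospitalisations sets the look-back: "the number of exacerbations of disease and cases of hospitalizations due to pulmonary disease during the past year will be asked". It then fixes the sources and time points: "This outcome will be assessed based on recall and clinical records at baseline, the 6th week and the 12th month". No shorter window, and no count since randomisation, is given for either follow-up time.

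Three other places bear on the reading:

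- **Outcome assessment** starts the clock at study entry: "Outcomes will be measured at baseline prior to the intervention, after 6 weeks and after 12 months from study entry".
- **Randomization** puts allocation after the baseline assessments: "The participants will then be randomized into control or intervention groups".
- **Sample size and statistical analysis** gives the general method: "Outcomes will be compared using ANOVA adjusted for baseline parameters". It also names t tests, chi-square tests and, if needed, non-parametric tests.

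The Fig. 2 legend lists "Number of exacerbations of the disease, hospitalizations and medications" as a visit item, and the usual-care section says "The participants in both groups will visit 12 times, at 1-month intervals". Neither attaches a different counting window.

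**The concern.** A look-back of one year suits the baseline interview. It also suits month 12, where the past year and the follow-up period roughly coincide. At week 6 it does not: a participant has then had at most six weeks in the allocated arm, and the other 46 or so weeks of the window were already counted at baseline. The week-6 figure is therefore mostly a second reading of the baseline figure.

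At stake is what the week-6 result can tell a reader. A report of yearly rates or their ratio at that visit would show the arms as nearly equal even if the programme halved events. A report of mean differences would carry avoidable noise. This is a window that the article states, not a detail left to a fuller document, and an analysis plan could correct it only if the events are dated.

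**Working it through.** **Inputs from the article.** Look-back of one year, taken as 365 days. Week 6 is 42 days from study entry, and randomisation comes after baseline assessment, so at most 42 days of the window follow randomisation. Sixty completers; equal allocation, hence 30 per arm, is assumed.

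**The article's own figure.** None is given for this outcome. The only calculated figure is for the primary outcome: "with an SD of 100, 90% power and a significance level of 5% requires 60 patients to complete the study", with improvements of 105 s and 20 s. Taking the 5% as two-sided:

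n per arm = 2 × (1.960 + 1.282)² × 100² / 85² = 29.1, rounded up to 30, or 60 in total.

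It reproduces and is untouched by this point. It supplies the 30 per arm used below.

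**Share of the window before randomisation.** (365 - 42)/365 = 0.885. The share after randomisation is f = 42/365 = 0.115. If randomisation falls some days after study entry, the first share is slightly larger.

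**Ratio scale.** With a constant underlying rate and a true rate ratio RR after randomisation, the past-year count shows 1 - f × (1 - RR):

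| True RR, weeks 0 to 6 | Apparent RR, past-year count |
|---|---|
| 0.70 | 1 - 0.115 × 0.30 = 0.97 |
| 0.50 | 1 - 0.115 × 0.50 = 0.94 |
| 0 (all events prevented) | 1 - 0.115 = 0.88 |

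**Difference scale.** Randomisation gives the pre-randomisation events the same expectation in both arms, so they cancel from the difference in means. With λ events per patient-year the expected difference is λ × f × (1 - RR) under either window. For RR 0.5 that is 0.058 events per patient at λ = 1 and 0.173 at λ = 3.

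**Noise.** Take Poisson counts with no treatment effect. The week-6 count shares a fraction 0.885 of its window with the baseline count, so after baseline adjustment its residual variance is λ × (1 - 0.885²) = 0.217λ. A count since randomisation has variance 0.115λ. The past-year window therefore nearly doubles the variance: 0.217/0.115 = 1.9.

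**Power.** I simulated 30 per arm with RR 0.5 in weeks 0 to 6, a linear model adjusted for the baseline past-year count, two-sided 5%, and 6,000 trials per setting. The event rates are assumptions, because the article gives none. Each cell shows Poisson counts first, then counts with extra between-patient variation (gamma-distributed rates, dispersion 1).

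| Events per patient-year | Past-year count | Count since randomisation |
|---|---|---|
| 1 | 7.4%, 7.0% | 10.5%, 8.9% |
| 2 | 10.4%, 9.6% | 17.9%, 15.4% |
| 3 | 13.8%, 12.5% | 24.0%, 20.4% |

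The average estimated difference was close to the true value under both windows. At λ = 3 the past-year count gave reductions of 0.173 and 0.166 and the since-randomisation count 0.172 and 0.165, against a true 0.173. The longer window causes no attenuation on this scale.

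**Month 12.** A one-year look-back then spans essentially the period since entry, so the share before randomisation is close to zero.

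**The case against.** The strongest reply is that the named analysis compares means with baseline adjustment, and on that scale the pre-randomisation events cancel. This stands. A reader might infer that the week-6 measure is biased to no effect, or cannot show an effect at all. The article does not support that: 11.5% of the window does follow randomisation, the mean difference is not attenuated, and the figures 0.94 and 0.97 apply only if results are expressed as ratios. The loss is one of precision.

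It can also be said that week 6 is too short to be informative under any window. That stands too: 9 to 24% power after the fix is still low. It limits the importance of the point but does not justify adding noise at no gain.

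Some wider readings are tempting and should be set aside:

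- *The health resource question is undermined.* The same section captures utilisation separately from central clinical records, with no past-year window attached.
- *Month 12 rests on long recall by participants who know their arm.* Clinical records are a stated source beside recall.
- *Weeks 0 to 6 are counted twice.* Any pair of counts that both start at randomisation does this; it is not a fault.
- *Counts are forced into ANOVA or a t test.* Non-parametric tests are allowed. The choice of a count model and the handling of early loss belong to an analysis plan that is not shown.

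Finally, the monthly visits may already record interval counts, which would make this mainly loose wording. That cannot be settled: the figure is not shown, and its legend does not say which visits the item marks. The section that defines the outcome gives only the past-year window.

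**Conclusion.** The point holds for week 6 only. As defined, about 88% of the week-6 window precedes randomisation and the count largely repeats baseline. The consequence is strong dilution if results are given as ratios (0.50 shown as about 0.94, 0.70 as about 0.97). On the stated baseline-adjusted comparison of means there is no bias, but already low power falls from about 9 to 24% to about 7 to 14%.

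The window share follows from the article alone. The dilution figures add a constant underlying event rate and illustrative true ratios. The power figures add 1 to 3 events per patient-year, a true ratio of 0.5 and 30 per arm.

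The outcome is secondary, month 12 is sound in this respect, and the primary outcome and its sample size are unaffected. This is a should-fix, not a threat to the trial's main conclusion.

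**What to change.** Restrict the past-year question to baseline and use that count as a covariate. Define the follow-up outcome as the number of events from randomisation to week 6 and from randomisation to month 12, tabulated from dated clinical records and, where they hold interval counts, from the visit records.

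The Trial status section says enrolment was completed in August 2018, so the week-6 interviews have probably taken place. The change can still be made before analysis by re-tabulating events by date. If some recalled events have no date, report how many and do not place them in the week-6 count by assumption.

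The cost is a few words in the outcome definition and some extra data tabulation. A count model with follow-up time as offset is a reasonable option, but the fix does not depend on it.

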### Data management

Patient data will be collected from their medical records, questionnaires completed by the questioner, test reports, documented physician comments, researchers’ observations and patient interview. A technician will enter the data from the ‘Case Report Form’ (CRF) into SPSS statistical software. To ensure the accuracy of data entry, double data entry will take place at every stage of data gathering.

The Coordinating Team, Steering Committee, Endpoint Adjudication Committee, Data Management Team and Data Monitoring Committee are responsible for the implementation, control and monitoring of the correct implementation of the study.

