## Discussion

This study using a controlled randomized clinical trial will investigate the impact of a PR programme on people with mustard gas lung disease. If the programme proves efficacious, pulmonary rehabilitation centres can be established and expanded across the country/countries that have been victims of chemical attacks.

Among the limitations of this study are the following: participation in the rehabilitation centre exercises for 6 weeks, three times a week might be difficult for those participants who are employed; and the length of the project (being 1 year long) raises the risk of participant drop-out.

Some of the strengths of this study are as follows: this is the first PR protocol that is being conducted for sulfur mustard victims; the emphasis on the use of objective and safe methods in assessing patients, instead of subjective methods, is an additional strength of this study; and the results of this study can be used in other regions that have also been victims of mustard gas exposure.

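### The exacerbation count rests partly on medicine-taking and on recall by participants who know their arm, so its between-arm comparison can be biased; at week 6 the past-year question also covers mostly pre-randomisation time

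*Protocol article*

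**What the plan says.** All references are to the Protocol article.

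- **Definition** (Number of disease exacerbations and hospitalizations): an exacerbation is "an increase in respiratory signs and symptoms leading to change in type and/or rate of medicine intake". The section does not say whether the change must be prescribed or may be the patient's own.
- **Look-back** (same section): "the number of exacerbations of disease and cases of hospitalizations due to pulmonary disease during the past year will be asked".
- **Source and timing** (same section): "This outcome will be assessed based on recall and clinical records at baseline, the 6th week and the 12th month". No rule says which source prevails when they disagree. Health resource use, by contrast, is taken from central clinical records alone.
- **Blinding** (Study design): "an assessor-blind, parallel-group, randomized clinical trial comparing PR with usual care". Outcome assessment adds that assessors do not know the allocation. Participants necessarily do.
- **Difference between arms** (Intervention group): "The pulmonary rehabilitation intervention will include a combination of physical exercises, an educational programme and psychosocial support". The Discussion describes "participation in the rehabilitation centre exercises for 6 weeks, three times a week". Background says that rehabilitation "also boosts COPD patients’ understanding of their condition and ability to self-manage". Controls receive usual medication and standard advice on activity.
- **Common to both arms** (Usual care; Follow-up): 12 visits at monthly intervals.
- **Committees** (Data management): "The Coordinating Team, Steering Committee, Endpoint Adjudication Committee, Data Management Team and Data Monitoring Committee" are listed as overseeing the study.

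**The concern.** Under this definition a worsening becomes a countable event only after somebody changes a medicine. That step is behaviour, and the intervention may alter it. A participant who has been taught about the condition, or who sees staff three times a week, may recognise and act on a worsening that a control participant would sit out. The same participant may instead manage it without any medicine change, or recall the year more favourably because of having received the active programme. The first path raises the rehabilitation count and the other two lower it. A masked interviewer does not help with recall, because the person answering is not masked.

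The second problem is one of timing. A question about the past year, asked six weeks after randomisation, mostly describes the year before it. Any early difference between arms is swamped by time that the intervention could not have affected.

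At stake is the interpretation of a secondary outcome. A difference could appear, shrink or vanish without a matching difference in disease.

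**Working it through.** **1. The plan's own figure.** The article gives no rate, variance or power for exacerbations. Its only sample-size figure concerns cycle endurance: difference 105 − 20 = 85 s, SD 100, 90% power, 5% level (two-sided and 1:1 allocation assumed).

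n per arm = 2 × (1.96 + 1.282)² × 100² / 85² = 29.1, rounded up to 30, so 60 in total. This reproduces (power 90.9% by the normal approximation, 89.9% by noncentral t). It does not bear on exacerbations, except that it gives 30 per arm for the steps below.

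**2. Contact.** Extra sessions: 6 weeks × 3 = 18, in the rehabilitation arm only. The extra-contact period is 42/365 = 11.5% of a year. Scheduled monthly visits are equal in both arms.

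**3. Week-6 look-back.** Taking week 6 from randomisation, the past-year window holds 52 − 6 = 46 weeks before randomisation: 46/52 = 88%. With equal rates before randomisation and a true rate ratio R afterwards, the ratio seen at week 6 is (46 + 6R)/52.

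- R = 0.80 appears as 50.8/52 = 0.977.
- R = 0.70 appears as 50.2/52 = 0.965.

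At month 12 the past-year window roughly matches the post-randomisation period, so this dilution belongs to week 6. It applies equally to the hospitalisation count, which shares the question.

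**4. Differential ascertainment (assumed inputs).** Let r be the ratio, rehabilitation to control, of the chance that a given worsening is counted. Then observed rate ratio = true rate ratio × r. A true 0.80 appears as 0.80 × 1.25 = 1.00 or as 0.80 × 0.8 = 0.64, depending on the sign of the distortion.

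For the false-positive rate with no true effect, assume λ = 1 to 3 events per patient-year, 30 per arm, one year of follow-up, and Poisson (k = 0) or negative binomial (k = 0.5) counts:

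SE = √[(1/λ + k)/30 + (1/(λr) + k)/30]; z = ln r / SE; P = Φ(−1.96 − z) + 1 − Φ(1.96 − z).

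Example: λ = 2, k = 0, r = 1.25 gives SE = √[(0.5 + 0.4)/30] = 0.173, z = 0.223/0.173 = 1.29, P = 0.251.

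| r | False-positive rate (nominal 5%) |
|---|---|
| 0.9 or 1.1 | about 6–11% |
| 0.8 or 1.25 | about 10–35% |
| 0.7 or 1.4 | about 18–68% |

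**5. Extra contact alone (assumed inputs).** Suppose a worsening is acted on with probability d under monthly contact and with certainty during the supervised weeks. With no true effect the rate ratio is 1/d for weeks 0–6 and 1 + 0.115 × (1/d − 1) over 12 months.

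- d = 0.8: 1.25 and 1.03.
- d = 0.5: 2.0 and 1.12.

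The contact effect is thus concentrated in the first six weeks and is small over the year.

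**The case against.** A reader might infer that the comparison is biased as a matter of fact, perhaps in a known direction, and that the definition should be replaced by records-only events. The documents do not support that, for these reasons.

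- **Sign and size are unknown.** Every value of r and d above is assumed. Recognition could raise the rehabilitation count, while self-management without a medicine change or favourable recall could lower it. A real fall in treated episodes would be a genuine effect, not an artefact.
- **The education content is not shown.** It is in Additional file 2. The remark on self-management in Background concerns COPD patients and does not mention adjusting medicines.
- **Safeguards exist.** Clinical records are a second source, assessors are blind and the monthly visits are equal. The Fig. 2 legend marks exacerbations, hospitalisations and medications separately from the main assessments, so they may already be collected monthly; the figure is not shown, so this cannot be settled.
- **Contact alone does little over a year.** The larger figure, ln(1.115) = 0.11, is below one standard error of the log rate ratio: under Poisson counts with 30 per arm, √[2/(30λ)] runs from 0.26 (λ = 1) to 0.15 (λ = 3).
- **Records are not neutral.** A recorded visit or prescription also depends on recognising a worsening and seeking care, and the programme is delivered at a hospital serving these patients.
- **It is a secondary outcome.** The primary endpoint and sample size are untouched, hospitalisations do not depend on the medicine rule, and resource use comes from records.

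These points rule out a finding of established bias and a records-only definition. They do not remove the risk. Assessor blinding cannot mask a participant's recall, and adding records to recall without saying which prevails leaves the recalled part in the count. The week-6 dilution does not depend on any of these points.

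**Conclusion.** The point holds as a risk, not as a demonstrated bias. The count depends on a medicine change by anyone and draws partly on past-year recall by participants who know their arm, while only one arm receives education and about 18 extra sessions. Differential ascertainment can therefore distort this comparison in either direction. Its size rests wholly on assumed inputs: a 10% ascertainment difference would matter little (false-positive rate about 6–11%), whereas a ratio of 0.8 or 1.25 would matter more (about 10–35%).

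The week-6 look-back is firmer, because it follows from the stated window and visit time: 88% of the period precedes randomisation, and a true rate ratio of 0.70 would show as about 0.97 if rates before randomisation are equal.

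Both problems deserve correction, in proportion to a secondary outcome.

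**What to change.** Keep the stated definition and change how events are counted and reported between arms:

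1. Count only events since randomisation, for week 0–6 and for week 0 to month 12. Keep the past-year question at baseline to describe prior history.
2. Where visits remain, ask about the time since the last visit, with identical questions in both arms.
3. Have the existing Endpoint Adjudication Committee classify, blind to arm, the events confirmed in the central clinical records. Report these separately from recall-only events.
4. Add a sensitivity comparison for week 6 to month 12, when scheduled contact is equal. This removes the extra-contact component but not any lasting effect of education or of knowing the allocation.

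**Cost.** Protocol or analysis-plan wording, plus modest work for a committee already named, on records already captured. No treatment changes.

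Timing limits item 2. Enrolment ended in August 2018 and the article appeared in February 2019, so every participant should already have been past week 6. Unless monthly questions were already being asked, early events would have to come from records and any dates already noted. Last visits were due in August 2019, so record review and blind classification were still feasible.

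The record-confirmed analysis will have fewer events and less precision. It still depends partly on care-seeking, so the change reduces recall bias without removing all ascertainment bias.
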